### Recruitment

Principal investigators from each center will have the task of presenting strategies to promote enrollment and to ensure the target sample size.

### Randomization and masking

Patients will be enrolled in this trial by gastroenterologists, surgeons, and endoscopists who will evaluate the cases in the inpatient wards or in the outpatient consultation areas. The participants will be randomized with a random-number table generated by an online platform.

A code list will be generated by randomization with a 1:1 randomization ratio, by blocks, stratified by centers and by American Society of Anesthesiologists’ classification (ASA) score. Each individual will be assigned a randomization code along with the treatment that corresponds. Once the patient meets the eligibility criteria and has provided informed consent, we will proceed to the allocation of each participant centrally, ensuring allocation concealment, and based on the randomization list. To prevent different subject recruitment rates at the various hospitals from interfering with the development of the study, the entire population will be randomized in blocks of four between the two treatment possibilities.

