## Methods/design

The PROMETHEUS trial is a randomized controlled, multicenter, prospective clinical trial with two parallel groups, without masking and with a 1:1 allocation ratio. One hundred and fourteen patients with WON will be scheduled for endoscopic ultrasound (EUS)-guided transmural drainage in nine tertiary Spanish hospitals and will be randomized to the LAMS and plastic-stent groups. All the centers are members of the Spanish Society of Digestive Endoscopy (SEED), which acts as the promoter of this trial.

Central ethical approval of the study protocol has been confirmed from the Comité Ético de Investigación Clínica (CEIC) del Hospital Universitari de Bellvitge-IDIBELL (ref approval no. 140/15) and we will not begin recruiting at other centers in the trial until local ethical approval has been obtained. A Standard Protocol Items: Recommendations for Interventional Trials (SPIRIT) Checklist is attached as Additional file 1.

**Table 1 Tab1:** Comparative table of the two kinds of stents used in transmural drainage of pancreatic collections

Lumen-apposing metal stent		Plastic	
Advantages	Disadvantages	Advantages	Disadvantages
Easy release	Expensive	Economical	Smaller diameter
Wide diameter	Less scientific evidence	Easy extraction	Shorter patency
Better drainage of solid waste and necrosis	Temporary placement	May be left permanently in place	High occlusion rate
Direct necrosectomy via stent	Traumatism caused by the ends	Greater experience (studies)	A single stent is not enough for WON
Longer patency	Not known whether permanent placement is possible	High success rate (> 80–90%, all types of collections)	Multiple > demanding technique (MTGT for WOPN)
Correct visibility			Worse visibility (fluoroscopy)
Short therapeutic time			
Hemostatic effect			
Prevents migration			Leakage of liquid (in ostomy)
Anchoring effect			
Prevents liquid leakage			Migration
Easy extraction			

*MTGT* Multiple transluminal gateway technique, *WOPN* Walled-off pancreatic necrosis

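### A single disclosed block size of four, within centre and ASA strata of an unmasked trial, lets a site know roughly 20–30% of allocations in advance; the block sentence also needs clearer wording

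*Protocol article*

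**What the plan says.** Under Methods/design, the protocol article describes a trial "with two parallel groups, without masking and with a 1:1 allocation ratio", with 114 patients in nine hospitals.

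Under Randomization and masking it says four things that bear on this point:

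- **Who enrols.** "Patients will be enrolled in this trial by gastroenterologists, surgeons, and endoscopists".
- **How the list is built.** Allocation is 1:1 and the list is made "by blocks, stratified by centers and by American Society of Anesthesiologists" class. The number of ASA levels is not given there. The Subgroup analysis section uses two ASA groups, but as printed both contain class II.
- **How concealment is claimed.** After eligibility and consent comes the "allocation of each participant centrally, ensuring allocation concealment, and based on the randomization list".
- **Block size.** The article states that "the entire population will be randomized in blocks of four between the two treatment possibilities". The reason it gives is that hospitals may recruit at different rates.

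Four is the only block size named. The article describes neither variation of the size nor any step to keep it from the sites.

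**The concern.** Concealment means that whoever decides to enrol a patient cannot know the next assignment. Central allocation keeps the list out of sight. In an unmasked trial, however, each site sees every stent it places and knows each patient's ASA class. With one known block size, the team can count within a stratum. After two patients on the same stent at the start of a block, the next two are known. After any three patients in a block, the fourth is known.

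The enrolling clinicians include endoscopists, and they have some freedom over when to refer and whom to approach. A known next assignment lets them match patients to the stent they favour. Two features leave the primary result exposed. Collection size bears directly on the 4-week outcome (Outcomes) but is not a stratification factor, and the main comparison is an unadjusted chi-square or Fisher test (Statistical analysis).

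The block sentence adds a second, smaller difficulty. It can be read as one block sequence over the whole trial, which does not fit the stratified list described just before it.

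**Working it through.** **Inputs.** Block size 4, 1:1, stratified by centre and ASA (Randomization and masking); N = 114 and 9 centres, no masking (Methods/design). Assumptions: equal centres, equally likely strata, and 1 to 4 ASA levels, since the number is not stated. The article gives no predictability figure to reproduce.

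**Step 1: one complete block.** A 2:2 block of four has 6 possible orders. The chance that an assignment is already fixed by earlier ones is 0, 0, 1/3 and 1 at positions 1 to 4.

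- Known with certainty: (0 + 0 + 1/3 + 1)/4 = 33.3%.
- Best guess (the arm that is behind so far in the stratum): (0.5 + 0.667 + 0.667 + 1)/4 = 70.8%, against 50% by chance.

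**Step 2: allow for unfinished blocks.** In a stratum of n patients the expected number of certain assignments is C(n) = (4/3) × (number of complete blocks), plus 1/3 if three patients are left over. With k strata, n is taken as Binomial(114, 1/k), and the share is (k/114) × Σ P(n) C(n).

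| Strata | Patients per stratum | Known with certainty | Best guess correct |
|---|---|---|---|
| 9 (centre only) | 114/9 = 12.7 | 30.0% (34 of 114) | 69.4% |
| 18 (two ASA levels) | 114/18 = 6.3 | 26.8% (31 of 114) | 67.9% |
| 27 (three levels) | 114/27 = 4.2 | 23.4% (27 of 114) | 66.4% |
| 36 (four levels) | 114/36 = 3.2 | 19.7% (22 of 114) | 64.7% |

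With two ASA levels split 60/40 to 80/20 instead of evenly, the share stays at about 27%.

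**Step 3: the other reading.** If blocks of four ran over the whole trial and each of nine equal sites saw only its own allocations, simulation gives about 0.4% known with certainty. The predictability problem therefore depends on blocks running within strata.

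**Step 4: illustration of what steering could do.** Assume that sites act on every certain assignment (27%) and choose patients whose chance of success is δ better for one arm and δ worse for the other. The false arm difference is 0.27 × 2δ. For δ = 5 points it is about 3 points and for δ = 15 points about 8. The design difference is 0.75 − 0.50 = 25 points (Sample-size calculation). The values of δ are assumptions.

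**Step 5: after the fix.** This assumes that the site knows which sizes are possible but not their order, with sizes equally likely. For a stratum of exactly six:

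- Fixed four: certain (0 + 0 + 1/3 + 1 + 0 + 0)/6 = 22.2%; best guess (0.5 + 0.667 + 0.667 + 1 + 0.5 + 0.667)/6 = 66.7%.
- Random 4, 6, 8: certain (0 + 0 + 0 + 0 + 0.010 + 0.048)/6 = 1.0%; best guess (0.5 + 0.613 + 0.613 + 0.776 + 0.610 + 0.776)/6 = 64.8%.

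| Scheme | Certain: stratum of six, then long run | Best guess: stratum of six, then long run |
|---|---|---|
| Fixed 4 | 22%, 33% | 67%, 71% |
| Random 2, 4, 6 | about 3%, 4% | about 69%, 70% |
| Random 4, 6, 8 | about 1%, 2% | about 65%, 68% |

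**The case against.** Four objections deserve weight.

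1. **One third is not this trial's figure.** A reader might take the complete-block value as the share of allocations that sites can predict. The documents do not support that. Sparse strata leave blocks unfinished and so lower predictability. In strata of exactly six it is 22%, and in strata of exactly three it is (1/3)/3 = 11%. This stands, and it is why the size here is put at about 20–30%.

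2. **The passage does not contradict itself.** A reader might infer that the entire-population sentence rules out stratification and leaves the arms unbalanced by centre and ASA. But stratification is stated outright just before it. The phrase can mean every patient, and the reason given, uneven recruitment across hospitals, fits blocks within centres. This also stands: it is an ambiguity. Nor can the two harms be added together. Predictability needs blocks within strata, and loss of balance needs blocks across the trial.

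3. **Varying the blocks does little for the best guess.** Favouring the arm that is behind needs no knowledge of block boundaries. Sizes 2, 4 and 6 leave the rate at about 69–70%, slightly worse than fixed fours in a stratum of six. This is correct, and it argues for leaving out blocks of two. It does not remove the large fall in certain prediction.

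4. **Steering is constrained.** Allocation follows eligibility and consent, so steering would have to happen before that. Stratifying by ASA limits steering by general sickness, so far as ASA captures it. That narrows the route but does not close it, because timing of enrolment and collection size remain open. Nothing in the documents shows that steering has occurred.

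**Conclusion.** The point holds at a moderate size. Followed as written, the scheme does not secure the concealment it claims. A site that tracks its own strata could know with certainty about 20–30% of the 114 allocations. The central figure is about 27% (31 patients), which assumes two ASA levels and equal centres. It also rests on blocks running within centre-by-ASA strata, the most plausible reading; under trial-wide blocks the share is near zero.

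The wording about the entire population is a lesser matter of clarity. The documents do not support calling it a contradiction, or saying that the arms are unbalanced by centre and ASA. The finding is a weakness that can be exploited, not evidence of bias. The change is worth making because it is cheap and removes nearly all certain prediction.

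**What to change.** - For allocations still to be made, issue a new central list with randomly varying block sizes, not disclosed to sites, within centre-by-ASA strata. Sizes 4, 6 and 8 are preferable to a set that includes 2. Define the ASA levels, without overlap, in the same place.
- Reword the block sentence to say that blocks run within centre-by-ASA strata, and keep the sizes out of any document the sites hold.

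The cost is a new list on the existing online platform and a short amendment. The statistical price is a slightly larger possible imbalance from unfinished blocks, which matters most if strata hold only three to six patients. The gain in the best-guess rate is small.

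The Trial status section has recruitment running from June 2017 to June 2020. If it has ended, the list cannot be changed. What remains is to correct the sentence and to disclose the list actually used, including whether its blocks ran within strata, so that readers can judge the risk of selection bias.

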### Procedural technique

#### Qualification of centers

The participation of a minimum of nine hospitals with an inclusion of about 13–15 patients per year per hospital is required. The investigators at the participating centers will all have experience in endoscopic intervention and therapeutics, previous experience in EUS-guided transmural drainage with metal and plastic stents (> 25 overall), and a minimum of 10 procedures per year, in addition to appropriate material at their disposal for carrying out transmural drainage with both types of stent.

#### General description of the technique

Each selected case will ensure a conclusive diagnostic revision with WON. In case of doubt, EUS-guided, fine-needle aspiration will be considered prior to drainage to rule out cystic tumor. Prophylactic antibiotic therapy will be administered in accordance with the protocol of each center. In case of INR > 1.5, this will be corrected in accordance with the protocol of each center until INR < 1.5. Procedures will be performed under deep sedation in accordance with the directives of each center. In case of collection > 10 cm (> 700 mL), tracheal intubation by anesthesiologist is recommended. Carbon dioxide insufflation is recommended, especially for endoscopic necrosectomy. The WON will be localized by using a linear echoendoscope, selecting the appropriate optimal region for carrying out the EUS-guided puncture. The collection will be punctured with a 19-G needle (plastic or LAMS group) or directly with an electrocauterizing device (freehand technique, only in the LAMS group). The guidewire will be advanced and coiled into the WON cavity. Then, the transmural ostomy will be carried out in accordance with the normal procedure of the experienced endoscopist. The use of a fluoroscope will be decided upon on the basis of technical considerations and the opinion of the endoscopic interventionist. The use (or not) of a fluoroscope will be noted in the case report form (CRF). The scale of the ostomy will be determined by the size of the collection (see Table 3).

**Table 3 Tab3:** Number of stents along with technical variations depending on size of WON, observed with EUS during procedure

Type	LAMS (*n*, ø)	Plastic (*n*, ø)
WON < 10 cm	1, 10–15–20 mm	≥ 1, minimum 1 of 10Fr (+ ostomy 8–10 mm)
WON > 10 cm	≥ 1, > 15 mm	≥ 2, minimum 1 of 10Fr (+ ostomy 10–15 mm)

*LAMS* lumen-apposing metal stent; *WON* walled-off necrosis, *FR* French

After the interventional procedure, all inpatients cases will be returned to the hospital ward and will discharged after clinical improvement. Outpatients will spend a minimal of 24 h under observation and will be discharged the next day unless there is no improvement of symptoms or the appearance of AEs.

#### Plastic-stent group

Double-pigtail plastic stents (5–10 cm in length, diameter 7–8.5 10 French gauge (Fr), Advanix, Boston Scientific, Spencer, USA) will be used. A minimum of one 10Fr pigtail plastic stent will be placed. After initial EUS-guided access, the ostomy will be dilated first, using a cystotome, and secondly with a balloon dilation. The plastic stent will be inserted and delivered following the routine technique of each interventional endoscopist. The number of the plastic stent and size of the balloon used to dilate the ostomy will depend on the WON size and content (see Table 3). The time to plastic stent withdrawal will be considered until total resolution by imaging. If there is pancreatic-duct involvement, non-withdrawal of stent will be considered.

#### Metal group

The metal stents used in this study will be LAMS (10, 15, or 20 mm in diameter, and 10 mm in length, HotAXIOS stent with an electrocautery-enhanced delivery system, Boston Scientific, Madrid, Spain). This is a self-expanding metal stent totally covered with luminal apposition. After the EUS-guided access into the WON using first a 19-G or directly with the electrocautery tip, the delivery system will be advanced into the cavity and the distal flange will be deployed under EUS guidance. Otherwise, the proximal flange will be released under EUS or endoscopic guidance. The time to stent withdrawal will depend on total resolution by imaging. However, there will be the intention to remove a LAMS no later than 4–6 weeks.

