#### Additional comments

In the event of technical failure in the placement of the stent (plastic or LAMS) for any reason, alternative treatment will be decided upon in accordance with the directives of the endoscopic interventionist, with the aim of offering the patient the best possible solution.

The first controls will be on the first day following and at 4 weeks (see Table 4). If there is no short-term clinical success, the most beneficial therapeutic approach for the patient will be adopted in accordance with the criteria of the patient’s medical team (for example: the use of technical variants at initial drainage such as placement of coaxial plastic pigtail within the LAMS, replacement or change the stent type, use of nasocystic drainage or other known variants).

**Table 4 Tab4:** Data management, calendar

Timepoint/stages	Study Period									
	Baseline	Intervention	24 h	7 days ±	4 weeks ± 3 days	8 weeks ± 5 days (Telephone)	16 weeks (4 months) ± 10 days	6 months ± 10 days (Telephone)	8 months ± 10 days	12 months ± 10 days (Telephone)
Enrollment										
Informed consent	X									
Clinical history and exploration	X									
Eligibility screen	X									
Allocation	X									
Intervention										
Implantation		X								
Removal					X					
INR		X								
Assessments:										
Blood test	X		X		X		X		X	
Imaging test	X	X			X	X^a^	X		X	
Symptomatology	X		X	X	X	X	X	X	X	X
Visit			X		X		X		X	
Telephone contact				X		X		X		X
Adverse effects	X	X	X	X	X	X	X	X	X	X
Primary outcome					X					
Secondary outcomes					X					
Medication	X	X	X	X	X	X	X	X	X	X

^a^Only in case of radiological clinical success but with persistence of the collection > 5 cm

Every intervention, diagnostic procedure, and additional therapeutic contribution will be noted in the CRF.

In the case of collections of significant size (i.e., 14 cm) with clinical-radiological success but without the disappearance of the collection (i.e., CTMD reduction from 14 to 6 cm), precluding the removal of the stent, a new CTMD will be performed at 4 weeks (8 weeks) to assess removal of the stent.

Therefore, the removal of a stent is contemplated when there is disappearance of the collection or a decrease < 5 cm.

Patients will remain in the hospital for a minimum of 24 h for clinical observation, under medical supervision.

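### The stent-removal passages conflict on timing (LAMS out by 4–6 weeks, or kept at least until an 8-week CT) and on the imaging criterion (complete resolution, or below 5 cm)

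*Protocol article*

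**What the plan says.** Four places in the protocol article govern when a stent comes out.

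- **Metal group:** "The time to stent withdrawal will depend on total resolution by imaging". The next sentence qualifies this: "there will be the intention to remove a LAMS no later than 4–6 weeks".
- **Plastic-stent group:** "The time to plastic stent withdrawal will be considered until total resolution by imaging". No time limit is given, and the stent may be left in place if the pancreatic duct is involved.
- **Additional comments:** for a large collection with clinical and radiological success but "without the disappearance of the collection (i.e., CTMD reduction from 14 to 6 cm), precluding the removal of the stent", the instruction is that "a new CTMD will be performed at 4 weeks (8 weeks) to assess removal of the stent". The section then concludes that "the removal of a stent is contemplated when there is disappearance of the collection or a decrease < 5 cm". It refers simply to the stent and limits neither statement to one arm.
- **Table 4:** the Removal row is marked only in the 4-week column. The 8-week contact has a window of ± 5 days. Its imaging is footnoted as applying only when there is success with a collection still above 5 cm, again with no arm named.

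Safety (early and late adverse events) and recurrences are secondary outcomes.

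**The concern.** A centre treating a LAMS patient like the protocol's own example (14 cm reduced to 6 cm) has two written instructions. One aims to have the stent out by week 6 at the latest. The other says that the residual rules out removal and that the question is reopened at week 8. No sentence says which prevails. Separately, a residual that is small but not zero satisfies one section's removal criterion and fails the other's.

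The document gives reasons to care about dwell time. Its Discussion lists severe delayed bleeding and buried stent among LAMS-related adverse events and presents clarifying LAMS safety as a purpose of the trial. With nine centres, different readings would produce different stent exposure within an arm. The adverse-event and recurrence results would then partly reflect which section was followed. Taking a stent out with some collection left, rather than after full resolution, could also bear on recurrence.

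**Working it through.** The plan gives no figure to reproduce. The check sets the sections side by side and applies calendar and size arithmetic.

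**1. Timing conflict (LAMS)**

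- Latest point of the intention in Metal group: 6 weeks = 6 × 7 = day 42.
- 8-week CT, from Additional comments and Table 4: 8 × 7 = 56, with ± 5 days, so 56 − 5 = day 51 to 56 + 5 = day 61.
- Gap: 51 − 42 = 9 days to 61 − 42 = 19 days after week 6.

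**2. Who is affected**

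- Under the primary outcome, success needs reduction to below 50% or below 5 cm, with clinical improvement.
- In the worked example, 6/14 = 0.43. This is below 50%, so the size criterion is met, and the 6 cm residual exceeds 5 cm.
- In general, a patient with success and a residual r > 5 cm must have qualified through the percentage criterion: r < 0.5 × B, where B is baseline size. Hence B > 2r > 10 cm.
- This assumes that 50% refers to the linear size in centimetres, as the worked example suggests. Taken on volume, the bound would be lower.
- Table 3 uses 10 cm to separate its two size classes, so these are not freak cases. The documents do not say how many patients fall above it.

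**3. Criterion conflict**

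Take a 4 cm residual at week 4, reading the threshold in Additional comments as a collection that has shrunk to below 5 cm.

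| | Stent-specific section | Additional comments |
|---|---|---|
| Plastic | Stays until complete resolution | Removal may be considered |
| LAMS | Not completely resolved, but intention to remove by 4–6 weeks | Removal may be considered |

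For LAMS both routes lead to removal by about week 6. For plastic they diverge. The Table 4 footnote gives this patient no 8-week imaging, because the residual is not above 5 cm. The next scheduled imaging is at 16 weeks ± 10 days: 112 − 10 = day 102 to 112 + 10 = day 122. The plastic stent could therefore come out around day 28, or stay until about days 102–122 unless unscheduled imaging is done.

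**4. Table 4**

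Removal is marked only at 4 weeks. It matches neither the 6-week end of the LAMS intention nor the removal decision planned for week 8.

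**The case against.** The strongest reply is that Metal group states an intention, not a limit, and that the 8-week CT is a specific exception to a general aim. The revision chronology supports this: the 8-week imaging legend was added deliberately in amendment 1. That is a fair reading, but the text does not state it. Metal group mentions no exception, and Additional comments does not say that it overrides the LAMS intention.

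Several stronger readings are tempting, and the documents do not support them.

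- A reader might count the delay from week 4 and obtain 51 − 28 = 23 to 61 − 28 = 33 days. That treats the lower end of a 4–6 week range as a deadline; only the gap after week 6 is defensible.
- A reader might say that LAMS stay in beyond week 8. The CT is there to assess removal, so the text supports only at least until that CT.
- A reader might say that the criterion mismatch leaves a LAMS patient with a 4 cm residual in limbo. The 4–6 week intention still applies to that patient.
- A reader might cite the comparative study in the Discussion as opposing the 8-week rule. Its advice on removal at 3 weeks is conditional on a resolved collection, and the 8-week rule concerns unresolved ones.
- A reader might infer a biased treatment comparison. Randomization is stratified by centre, so differing readings do not confound allocation. They add variation in exposure and blur which removal strategy is being compared.

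Two mitigations stand in part. The coordinating centre is to settle doubts and limit heterogeneity, and interventions are already noted in the CRF. Neither tells a centre which written rule to follow. Nor is this detail lost in condensing a fuller protocol: the statements printed here disagree.

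**Conclusion.** The removal passages are inconsistent in current operative text and need reconciling. For LAMS patients with success and a residual above 5 cm, the sections differ by at least 9–19 days of dwell time, measured from week 6 to the 8-week CT. This subset has baseline collections above about 10 cm, on the assumption that 50% means half the original linear size. For plastic stents with a residual below 5 cm, the choice of section can move removal from about week 4 to the 16-week imaging.

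The consequence falls on dwell time and on secondary outcomes: adverse events, especially late ones, and recurrences. The 4-week primary outcome is little affected, because it is read at about the time removal is first decided. The documents give neither the number of patients concerned nor adverse-event rates by dwell time, so the effect on the safety comparison cannot be computed. The point merits correction but does not threaten the main result.

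**What to change.** Reconcile Metal group, Plastic-stent group, Additional comments and Table 4 (Removal row and footnote) into one consistent removal rule per arm. The rule should state:

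- whether the 8-week exception applies to LAMS, and if so that it takes precedence over the 4–6 week intention;
- which imaging finding triggers removal in each arm, in the same words everywhere.

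The choice of rule belongs to the clinical team; this review takes no position on it. In the analysis, report stent dwell time by arm beside the adverse-event results, using removal dates from the interventions already noted in the CRF.

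The cost is a clarifying amendment and a note to the centres. No new procedures are needed, and little or no new data.
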